### Primary outcome measure

The primary outcome measure is the change in depressive symptoms as measured with the CES-D [37]. This questionnaire is designed to measure depressive symptoms in the general population (i.e., persons older than 18, without psychiatric disease). The 20-item scale measures the major components of depressive symptomatology, including depressive mood, feelings of guilt and worthlessness, psychomotor retardation, loss of appetite, and sleep disturbance. Participants are asked to indicate if they feel a particular item is applicable to their situation of the past week, on a 4-point scale. Scores range between 0 and 60, with higher scores indicating more depressive symptoms. In the general population, the usual cut-off score for depression is ≥16. Within cancer patients, the CES-D has yielded good psychometric properties, with good construct validity, good internal consistency and proper test-retest reliability [40].

### Secondary outcome measures

#### Suicidal intent (BSS)

The Beck Scale for Suicide Ideation (BSS) [38] is a 21-item self-report instrument for detecting and measuring the current intensity of the patients’ specific attitudes, behaviors, and plans to commit suicide during the past week. The first 19 items consist of three options graded according to the intensity of the suicidal intent and rated on a 3-point scale ranging from 0 to 2. These ratings are then summed to yield a total score, which ranges from 0 to 38. The last two items assess the number of previous suicide attempts and the seriousness of the intent to die associated with the last attempt. In this study, only the first 19 items are administered. If the patient reports any active or passive desire to commit suicide on the first 5 screening items, then the additional 14 items are administered as well.

#### Health-related quality of life (SF-36 and EQ-5D)

HRQOL is assessed by means of the Short-Form Health Survey (SF-36) [41]. The SF-36 is composed of 36 items, organized into 8 multi-item scales assessing: (1) physical functioning; (2) role functioning-physical; (3) role functioning-emotional; (4) pain; (5) vitality; (6) social functioning; (7) mental health; and (8) general health perceptions. Scores range from 0-100. Furthermore, two higher-order summary scores can be computed – one for physical health (Physical Component Summary) and one for mental health (Mental Component Summary). On these scales, scores have a mean of 50 and a standard deviation of 10 based on data from the general population.

In addition, the EuroQol (EQ-5D) [42] is administered. This is a standardized, non-disease specific instrument assessing HRQOL. With 5 items scored on a 3-point Likert type scale, the EQ-5D measures mobility, self-care, usual activities, pain/discomfort and anxiety/depression.

#### Brain tumor-specific HRQOL (EORTC BN20)

For glioma patients, a supplementary questionnaire module is employed to assess additional health problems associated specifically with brain tumors and their treatment. The EORTC Brain Cancer Module (BN20) [43] is organized into multi-item subscales assessing future uncertainty, visual disorders, motor dysfunctions, and communication deficits. The remaining 7 items assess other disease symptoms and side-effects of treatment found to be prevalent among patients with brain tumors, including headaches, seizures, drowsiness, hair loss, itching, weakness in the legs, and lack of bladder control. The scores range from 0-100, with higher scores indicating more symptoms.

#### Fatigue (CIS)

Fatigue and fatigue related symptoms are measured with the Checklist Individual Strength (CIS) [44]. The CIS is a multidimensional fatigue scale; it measures fatigue severity (8 items), concentration problems (5 items), reduced motivation (4 items), and reduced activity (3 items). Each item is scored on a seven-point Likert scale. Total scores of every subscale are obtained by adding the individual items, with high scores indicating a high level of fatigue, a high level of concentration problems, low motivation, and a low level of activity. Based on data from patients with chronic fatigue syndrome, patients with a score of >35 on the fatigue severity subscale are considered to be severely fatigued.

#### Cognitive functioning

Patient’s self-reported cognitive functioning is rated by the scale developed for use in the Medical Outcomes Study [45]. This 6-item scale assesses day-to-day problems in cognitive functioning including difficulty with reasoning and problem solving, slowed reaction time, forgetfulness, and problems with concentration (range 1-6).

#### Costs (TIC-P)

Costs in terms of health care utilization and production loss are assessed with the Trimbos/iMTA questionnaire for Costs associated with Psychiatric Illness (TIC-P) [46]. This questionnaire consists of two parts; part 1 covers the direct costs of care utilization of participants (15 items), and part 2 is used to determine indirect costs that result from production loss associated with the psychiatric symptoms. Here, the Short Form Health and Labor Questionnaire [47] is incorporated. This questionnaire contains three modules that assess the absence from paid employment, production loss without absence from paid employment, and impediments to paid or unpaid employment.

#### Patient satisfaction

During the post-intervention assessment (T1 or T3), the patients’ experience with the online course is evaluated. A short study-specific questionnaire evaluating the usability, readability, course content, and self-perceived usefulness of both the online course and the feedback provided by the coach is presented along the other questionnaires. Room for remarks is provided as well.

### Statistical analyses

Appropriate parametric and non-parametric statistical tests will be employed to examine differences between the groups in terms of all relevant demographic and clinical variables at baseline. Missing observations at follow-up will be imputed using the multiple imputation procedure [48]. Following the CONSORT guidelines, the intention-to-treat principle will be applied. All randomized participants will be included in the analyses, regardless of how many treatment modules or sessions they complete. Within-group and between-group differences (e.g., patients with or without epileptic seizures, pain, neurological deficits, or self-reported cognitive deficits) in dependent variable scores will be analyzed using both univariate and multivariate statistical techniques. For between-group statistical comparisons, sociodemographic variables (age, gender, and education) will be used as covariates, where necessary. The effects of the interventions will be tested by means of Helmert contrasts. Relative improvements in depressive symptoms (CES-D score) in the experimental group compared with pre-treatment assessment as well as both control groups will be calculated using Cohen’s d. If the primary outcome measure is non-normally distributed, the test and the 95% confidence intervals will be based on robust standard errors and/or on non-parametric bootstrap techniques. This will help to correctly ascertain the relative effectiveness of the treatment over the control conditions.

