### Randomization

Glioma patients are randomly assigned to either the intervention group or the waiting list control group after completion of the baseline assessment (T0). An adaptive simple randomization technique is employed to minimize the chance of imbalanced group sizes.

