### Sample size

The effect of the intervention on symptoms of depression is the primary outcome measure and this is used as starting point for the sample size calculations. Based on previous experience with this intervention in adults, we expect a Cohen’s d of 0.50. Assuming an alpha of 0.05 and a statistical power (1-beta) of 0.80, we need 50 patients in each condition. Allowing for a dropout percentage of 25% once included, we aim to recruit 126 glioma patients (63 per group) and 63 patients with haematological malignancies in total.

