## Discussion

In this paper, we describe the study design of a randomized controlled trial aimed at evaluating the effects of an internet-based, guided self-help intervention for depressive symptoms in glioma patients. This study is innovative in two ways: 1) as of yet, there is no evidence from RCTs for the effectiveness of psychotherapy in glioma patients with depressive symptoms; and 2) to our knowledge, providing psychosocial care through the internet has not been explored in the depressed glioma patient population until now.

We expect the external validity of this study to be high, as we employ only few exclusion criteria. Any adult WHO grade II, III or IV glioma patient at any disease stage with mild depressive symptoms is invited to participate in the trial to try and relief these symptoms. Furthermore, as the intervention is administered through the internet and patient inclusion is organized nation-wide, we should be able to reach a large group of potential participants. Using the internet also evidently has its downsides. For certain patients, such as those unaccustomed to using the computer in their everyday lives or those with more severe cognitive impairment, using the internet may prove more difficult and could possibly result in non-participation or dropout of the study. We aim to construct the website in a very straightforward and easy-to-use way, in order to minimize this possibly negative effect. In addition, both interventions using the internet and self-help interventions are prone to high dropout rates [49], suggesting that this problem could occur in our trial as well. Therefore we present the online questionnaires separately from the intervention website, and email reminders are sent for both the assessments and the course assignments separately. Moreover, if participants do not respond to these reminders, we try and contact them through telephone instead. This should strengthen the relationship between the participants and the researchers substantially, thereby possibly improving patient participation throughout the trial [50].

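### The stated covariate rule omits baseline CES-D and gives no criterion for adjustment, so the primary comparison gives up precision that ANCOVA would provide at no cost in data

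*Protocol article*

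**What the plan says.** All places are in the protocol article.

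- **Primary outcome measure:** "The primary outcome measure is the change in depressive symptoms as measured with the CES-D".
- **Statistical analyses, covariates:** for between-group comparisons, "sociodemographic variables (age, gender, and education) will be used as covariates, where necessary". No rule says when adjustment is necessary, and neither baseline CES-D nor any clinical variable is in the list.
- **Statistical analyses, test:** "The effects of the interventions will be tested by means of Helmert contrasts". The model in which the contrasts are formed is not named.
- **Statistical analyses, baseline:** a separate sentence plans to "examine differences between the groups in terms of all relevant demographic and clinical variables at baseline".
- **Randomization:** glioma patients are allocated once T0 is complete, so each has a pre-randomisation CES-D. "An adaptive simple randomization technique is employed to minimize the chance of imbalanced group sizes"; no balancing on CES-D or on disease factors is described.
- **Sample size:** "we expect a Cohen’s d of 0.50", with alpha 0.05, power 0.80, 50 patients per condition, and 63 per group after allowing for 25% dropout. The article does not say which SD d refers to, or whether alpha is one- or two-sided.

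**The concern.** An article may leave model details to a fuller document. This one does state a covariate rule, and the rule is weak in two ways.

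First, the list leaves out the outcome itself measured at T0, the most obvious candidate to predict follow-up CES-D. Subtracting the baseline imposes a slope of 1 on it. ANCOVA estimates the slope, which lowers the variance and removes the dependence on chance baseline differences that a change score keeps whenever the true slope is below 1.

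Second, an adjustment made only as needed, with need undefined, lets the adjustment set for the primary comparison be settled after the data are seen.

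At stake is power in a trial that expects about 47 evaluable patients per arm, and a primary estimate that does not depend on a later choice.

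**Working it through.** **Inputs.** From Sample size: d = 0.50, alpha 0.05, power 0.80, 50 per condition, 25% dropout, 63 per group. Assumed, because the article gives no figure: r, the correlation between T0 and follow-up CES-D, at 0.3, 0.5 and 0.7; equal SDs at the two times; two-sided alpha; and the SD to which d refers (both readings are shown).

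**1. The plan's own figures.** n per arm = 2(z_alpha + z_beta)²/d².
- One-sided: 2(1.645 + 0.842)²/0.25 = 49.5, so 50. This reproduces the article.
- Two-sided: 2(1.960 + 0.842)²/0.25 = 62.8, so 63.
- Dropout: 50 × 1.25 = 62.5, so 63 recruited per group. Then 63 × 0.75 = 47.25, about 47 evaluable.

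**2. Variance.** With the score variance set to 1, a change score has variance 2(1 − r) and ANCOVA has 1 − r². The ratio of ANCOVA to change score is (1 − r²)/(2(1 − r)) = (1 + r)/2.

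| r | Change score, 2(1 − r) | ANCOVA, 1 − r² | Ratio |
|---|---|---|---|
| 0.3 | 1.40 | 0.91 | 0.65 |
| 0.5 | 1.00 | 0.75 | 0.75 |
| 0.7 | 0.60 | 0.51 | 0.85 |

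Read the other way, the change score carries 54%, 33% and 18% more variance.

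If the SDs differ (s0 at baseline, s1 at follow-up), the change-score variance minus the ANCOVA variance is s0² + s1² − 2r·s0·s1 − s1²(1 − r²) = (s0 − r·s1)². This is never negative, so ANCOVA does not lose, though the size of the gain would change.

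**3. Power at 47 per arm, two-sided t-test.**

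*Reading A: d = 0.50 on the SD of the score.* The effective d is 0.5/√(2(1 − r)) for change and 0.5/√(1 − r²) for ANCOVA.

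| r | d, change | Power | d, ANCOVA | Power |
|---|---|---|---|---|
| 0.3 | 0.423 | 0.527 | 0.524 | 0.710 |
| 0.5 | 0.500 | 0.669 | 0.577 | 0.791 |
| 0.7 | 0.645 | 0.872 | 0.700 | 0.919 |

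*Reading B: d = 0.50 on the SD of the change.* The effective d is 0.5 for change and 0.5/√((1 + r)/2) for ANCOVA.

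| r | Power, change | d, ANCOVA | Power |
|---|---|---|---|
| 0.3 | 0.669 | 0.620 | 0.845 |
| 0.5 | 0.669 | 0.577 | 0.791 |
| 0.7 | 0.669 | 0.542 | 0.739 |

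The gain is 18, 12 and 5 points under A, and 18, 12 and 7 under B.

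**4. WHO grade.** The article gives no association between grade and CES-D. If grade explained an assumed 2%, 5% or 10% of the outcome variance, the two-sided requirement of 63 per arm (normal approximation) would fall to 62, 60 or 57.

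**The case against.** **Baseline is already used.** This is correct: change from T0 uses it by subtraction. The complaint is therefore one of efficiency, change score against ANCOVA, and not an unused measurement.

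**The covariate sentence may not govern the primary test.** It follows a sentence on comparisons such as patients with and without seizures, and the intervention effect has its own sentence on Helmert contrasts. The model behind those contrasts could contain a baseline term, and the Discussion mentions a further possible adjustment for outside care recorded by the TIC-P. This leaves real uncertainty about the intended model. It does not remove the point: the rule is written for between-group comparisons in general, and nothing in the article names T0 CES-D as a covariate.

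**The magnitude rests on assumptions.** It does. Neither r nor the SD behind d is given. The direction of the gain is the same on both readings of d; its size is not fixed by the document.

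**Stronger readings that the text does not support.**
- A reader might infer that significance tests at baseline decide which covariates enter, because the section also says that "tests will be employed to examine differences between the groups in terms of all relevant demographic and clinical variables at baseline". The two sentences are not linked, and they cover different variables. The groups compared may also include the non-randomised haematological group, where such a comparison has a purpose. What can be said is that the trigger is undefined.
- A reader might take WHO grade to be the key missing prognostic factor, since "Any adult WHO grade II, III or IV glioma patient at any disease stage" may enter. The article gives no figure linking grade to CES-D. The Background calls the cause of depression unclear, and the mechanisms it lists do not include grade. A loss from omitting grade is not shown, and allocating without balancing on it is not an error.

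**Conclusion.** The point holds as one of efficiency and pre-specification. The stated covariate rule leaves out T0 CES-D and attaches an undefined condition to the covariates it does name. As described, the analysis uses the baseline by subtraction only, and ANCOVA would have 0.65 to 0.85 of that variance for r between 0.3 and 0.7. At about 47 evaluable patients per arm this is worth roughly 5 to 18 percentage points of two-sided power, depending on r and on the SD behind d.

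These figures assume equal SDs at the two times, and they treat 25% dropout as a plain loss of patients, without crediting the planned multiple imputation. The point does not show bias in the planned comparison, nor any fault in the allocation.

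**What to change.** State that the randomised comparison of CES-D, at whichever time point is primary, is analysed by ANCOVA or an equivalent mixed model with T0 CES-D as a fixed covariate. Replace the conditional rule with a covariate set named in advance and used whatever imbalance is seen; age, gender and education can stay in it. WHO grade may be added as an optional pre-specified covariate, on the understanding that the document does not show how much it would gain.

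The cost is a change of analysis wording. T0 CES-D is already collected from every randomised patient, and the article says the trial is still recruiting, so the rule can be fixed before the outcome data are analysed. Neither the allocation procedure nor the assessments need to change.

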## Methods/design

### Design

This study is a randomized controlled trial evaluating the effects of an internet-based guided self-help course for depressive symptoms in glioma patients. We compare a group of patients who receive the intervention with a three month waiting list control group and a non-central nervous system malignancy control group. The intervention, which takes approximately 5 weeks to complete, is aimed at patients with mild to moderate depressive symptoms.

Assessments include self-reported outcomes completed online. The assessments are scheduled at baseline (T0), after completion of the online course (approximately 6 weeks after baseline; T1), 12 weeks after baseline (T2), and 12 months after baseline, see Figure 1. Those in the waiting list control group receive the same assessments, but are also assessed after completion of the online course (T3; approximately 6 weeks after T2), and 12 weeks thereafter (T4). Furthermore, patients with a high-grade malignancy undergo an additional assessment at 6 months after baseline (T3 or T5), as is also depicted in Figure 1. This study is performed in accordance with the Declaration of Helsinki.

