### Intervention

The internet-based guided self-help intervention is based on the principles of problem solving therapy. The original intervention, ‘Everything under control’ (“*Alles onder controle*”) has been shown to have significant positive effects on depression, anxiety and stress/burnout in a randomized controlled trial with 215 adults from the general population [39]. With small changes, this online intervention is adapted for use by glioma patients and patients with haematological malignancies. Modifications concern additional information about the specific diseases and their treatment, and the psychological impact on everyday life. Examples of participants’ assignments are made disease-specific.

The intervention consists of 5 modules with text and exercises. Patients are asked to complete one module a week and spend a minimum of two hours a week on their exercises. During the intervention, patients describe what they feel is important in their lives, make a list of their problems and concerns, and divide these into three categories: 1) unimportant problems (problems that are not related to what is important in their life), 2) important and solvable, and 3) important but unsolvable. For each of these problems the patient makes a plan on how to cope with this, guided by methods explained in the modules. The participants receive feedback on the exercises from a personal coach within three working days after completion of the assignment. The coach is not a therapist, but only supports the patient in working through the intervention. Participants can always contact their coach for additional support through the website. The coaching is provided by one of the researchers ([name]), by trained and supervised students in the final phase of a Master’s program in Psychology or by specialists from Prezens. In collaboration with the VU University medical center, Prezens provides psychological care and support.

The glioma patients in the waiting list control group are offered the same intervention after completion of the 12 weeks follow-up (T2).

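### The only named test of the intervention effect, Helmert contrasts, has no stated factor, level order or primary contrast, and on the natural three-group reading two of the three arrangements omit the randomised comparison

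*Protocol article*

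**What the plan says.** The protocol article names one test for efficacy, in Statistical analyses: "The effects of the interventions will be tested by means of Helmert contrasts". The factor, the order of its levels and the contrast that carries the primary conclusion are not given.

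The next sentence plans Cohen's d for improvement "in the experimental group compared with pre-treatment assessment as well as both control groups". The section closes on the aim of the analysis: "This will help to correctly ascertain the relative effectiveness of the treatment over the control conditions". For between-group comparisons, "sociodemographic variables (age, gender, and education) will be used as covariates, where necessary".

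The groups are set out elsewhere:

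- Design compares the intervention group "with a three month waiting list control group and a non-central nervous system malignancy control group".
- Randomization covers two of these three groups: "Glioma patients are randomly assigned to either the intervention group or the waiting list control group".
- Intervention says that "this online intervention is adapted for use by glioma patients and patients with haematological malignancies", and that the waiting list is offered the course after the 12-week assessment (T2).
- Sample size rests on one effect, d = 0.50, with 50 patients per condition. It recruits 63 per glioma group and 63 haematological patients.

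**The concern.** A Helmert set on three levels has two contrasts: one level against the mean of the other two, then those two against each other. Which comparisons are tested depends entirely on which level stands alone. The only comparison protected by randomisation is intervention versus waiting list in glioma, and the text does not secure it.

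The wording about two control groups and plural control conditions fits best with isolating the intervention group and averaging the two controls. That arrangement gives half the comparator's weight to patients with another disease who were not randomised and who apparently take the same course. If they improve, the apparent benefit in glioma shrinks. If the waiting list is isolated instead, their improvement is credited to the intervention. Adjusting for age, gender and education does not remove a difference by diagnosis.

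At stake is whether the named test answers the trial's question: does the course reduce depressive symptoms in glioma patients?

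**Working it through.** **The plan's own figure.** The normal approximation for two groups is n = 2(z_alpha + z_beta)²/d². With d = 0.50 and power 0.80:

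- one-sided 5%: 2(1.645 + 0.842)²/0.25 = 49.5, so 50 per group;
- two-sided 5%: 2(1.960 + 0.842)²/0.25 = 62.8, so 63 per group.

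The stated 50 is therefore reproduced as a one-sided comparison of two groups. This is a separate matter, but it explains why the direct contrast below has two-sided power 0.705 and not 0.80. It also shows that the trial was sized for a pairwise comparison.

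**Inputs.** d = 0.50 and n = 50 per group are from Sample size. The SD is set to 1, the test is two-sided at 5%, and power is by normal approximation. Means are improvements relative to waiting list: intervention d, waiting list 0, haematological group h. The documents do not give h, so it is assumed to lie between 0 and 0.75.

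**The three arrangements.** For a contrast with weights c, the expected value is the weighted sum of the means and SE = √(Σc²/n).

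1. *Intervention isolated.* The first contrast, weights (1, −½, −½), has expected value d − h/2 and SE = √(1.5/50) = 0.173. The second is waiting list versus haematological.
2. *Waiting list isolated*, signed for benefit. The first contrast, weights (½, −1, ½), has expected value (d + h)/2 and SE 0.173. The second is intervention versus haematological.
3. *Haematological group isolated.* The first contrast is not a treatment effect. The second is intervention versus waiting list, with expected value d and SE = √(2/50) = 0.200.

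Only arrangement 3 contains the randomised comparison.

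**Results with a true glioma effect, d = 0.50** (expected value; power)

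| h | Intervention vs mean of both controls | Waiting list vs mean of the other two | Intervention vs waiting list |
|---|---|---|---|
| 0 | 0.50; 0.82 | 0.25; 0.30 | 0.50; 0.705 |
| 0.25 | 0.375; 0.58 | 0.375; 0.58 | 0.50; 0.705 |
| 0.50 | 0.25; 0.30 | 0.50; 0.82 | 0.50; 0.705 |
| 0.75 | 0.125; 0.11 | 0.625; 0.95 | 0.50; 0.705 |

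**Results with no glioma effect, d = 0** (expected value; rejection rate)

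| h | Intervention vs mean of both controls | Waiting list vs mean of the other two | Intervention vs waiting list |
|---|---|---|---|
| 0 | 0; 0.05 | 0; 0.05 | 0; 0.05 |
| 0.25 | −0.125; 0.11 | 0.125; 0.11 | 0; 0.05 |
| 0.50 | −0.25; 0.30 | 0.25; 0.30 | 0; 0.05 |
| 0.75 | −0.375; 0.58 | 0.375; 0.58 | 0; 0.05 |

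With 63 analysed per group the pattern is the same. At d = 0.50, the first contrast of arrangement 1 has power 0.90, 0.68, 0.37 and 0.13 across the four values of h, against 0.80 for the direct contrast.

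**The case against.** The article does not say that the contrasts run over the three groups. Assessments are repeated, and Helmert contrasts can be taken over time. Even over groups, the analyst chooses the order. Isolating the one non-glioma, non-randomised group is a sensible choice, and it leaves the randomised contrast intact. Two arrangements out of three is a count, not a probability. The sample size fits a pairwise comparison, and the Cohen's d sentence can be read that way too. Contrast coding could also be settled in a fuller document that is not shown.

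Much of this stands. A reader might infer that the plan commits to averaging the haematological group with a randomised arm, and so has an invalid primary test. The text does not support that, because neither factor nor order is fixed. A reader might also take it as established that haematological patients follow the course. The article says that the course was adapted for their use, which indicates this strongly, yet it calls them a control group, and the participant-flow figure is not shown.

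The point itself remains. The article does choose a method, and it is the only test of effect that it names. Cohen's d is an effect size and is planned against both control groups alike, so it does not single out the randomised comparison. Reading the contrasts over time does not settle the matter either: the 12-month assessment comes after the waiting list has been offered the course, and the randomised contrast would still be unnamed. If the haematological patients did not use the course, they would still be a non-randomised group with another disease, and nothing would make h zero.

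**Conclusion.** The concern holds as a badly fixed primary test, not as a demonstrated invalid one. As written, the named method need not estimate the randomised treatment effect, and the group coding that best matches the surrounding wording does not contain it.

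For d = 0.50, 50 per group and two-sided 5%, that coding estimates between 0.50 and 0.125 as h goes from 0 to 0.75, with power from 0.82 to 0.11. Isolating the waiting list can instead give false positives: about 30% rejection at h = 0.5 with no glioma effect. The direct contrast is unaffected by h, with 5% size and power 0.705.

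These sizes rest on the three-group reading and on an assumed h, and no single figure is a forecast. In particular, 30% should not be read as the trial's power. It belongs to one coding at d = h = 0.5. At h = 0 that coding loses nothing, and with the waiting list isolated there is no dilution when h = d.

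**What to change.** Replace the Helmert sentence with one primary contrast: change in CES-D, intervention versus waiting list, among randomised glioma patients, using assessments up to T2, before the waiting list is offered the course. Keep the haematological group out of that test.

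State whether the haematological patients follow the course. Report change in treated glioma versus haematological patients separately, labelled as a non-randomised comparison by diagnosis, and drop the description of it as effectiveness over a control condition. Label the Cohen's d against that group in the same way.

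The cost is a few sentences in Statistical analyses. No patients, assessments or data need to be added.
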